**10. Ethical aspects**

a) General principles:

The trial will be carried out in compliance with the principles enshrined in the Declaration of Helsinki (Annex IV), and in compliance with current legal standards (Royal Decree 561/1993 of 16 April), and will not begin until the appropriate approval/authorisation has been granted by the CEIC, the Institute’s Director, and the national medication agency (Agencia Española del Medicamento).

b) Informing subjects:

Patients will be informed orally and in writing, and all participants will receive all of the relevant information adapted to their level of understanding.

(See Annex II: Patient information sheet, and Annex III: Informed consent form).

c) Confidentiality:

The patient will be informed that their participation in the trial will be treated with the same confidentiality as their clinical documentation, but that, where necessary, access may be granted to a member of the CEIC of the centre, a designated health authority inspector, or the clinical trial supervisor.

In the DCN, patients will only be identified by their initials and their patient inclusion number for the study.

The name of the patient will not appear in any publication or communication of the results of the study.

The participation of the patient in the test will be reflected in his/her clinical history.

The investigator will compile a list containing the names of patients taking part in the trial, their inclusion number, and their clinical history.

d) Trial safety:

The trial promoter has taken out a civil liability insurance policy that covers all liabilities for damage entailed by carrying out the current trial.

***

**11. Practical considerations**

a) Responsibilities of participants:

The main researcher will review and approve the trial protocol, request authorisation from the CEIC, as well as the agreement of the Director of the Institute, sign the research commitment form; the main researcher also bears the responsibility for reviewing and adopting the final clinical trial report.

Other members of the research team will undertake the patient eligibility evaluation, inform patients and their representatives, request written consent, evaluate the efficacy and safety of treatment, complete and sign the CDN and carry out follow-up of adverse events.

The researchers are responsible for fulfilling the requirements of the protocol.

The supervisor will ensure that data included in the CDN corresponds with the data in the clinical history and that patients have been appropriately informed and included in the treatment group to which they were assigned through a random means.

b) Storage, handling, processing and correcting data:

The main researcher will possess a file containing the following information: basic drug information, trial protocol, the Declaration of Helsinki, CDM template, patient information sheet template, informed consent form, adverse events notification form and a list of patients included in the trial.

1. Identification and labelling of samples for clinical trials:

The samples of the drug under investigation will be used in their commercial presentation.

1. Publication:

Investigators will publish the results of the study in internationally indexed journals.

***

**12. Statistical analysis**

a) Statistical tests:

- Descriptive analysis:

The descriptive analysis will include variables referring to demographic data and clinical events related to the sample as well as adverse reactions in terms of absolute and relative frequency, means and standard deviations, medians and ranges.

*Indications for antiretroviral treatment*

Spanish recommendations for ART (27) prescribe that it should not be given to patients who are asymptomatic with CD4+ lymphocyte cell count <500 µg/L and a viral load <10,000 copies/mL. The proportion of patients presenting both criteria will be determined at two points: 1) when VL reaches the set-point following the last withdrawal from treatment; and 2) at the end of the study (week 120-136).

- Comparative Analysis

*1) Increase in plasma VL in the* ***eighth*** *week following withdrawal, and 2) proportion of patients with cytotoxic response to HIV.*

- Comparison will be made between cycles one, two, three and four.

An increase in VL is defined as being at least three times greater than the baseline (prior to ART) (corresponding approximately to an increase of 0.5 log).

- In patients with a VL <10 copies/mL (undetectable), an increase will be considered as being any value >20 copies/mL after two weeks since the interruption of treatment.

- A more sensitive analysis will compare the second, third and fourth cycles with the first cycle, for each patient, as paired data. McNemar’s test will be used to compare discordant results: i.e., N pairs with a higher value for the first cycle and a lower value for the fourth cycle, with the N pairs from the opposite situation. The same considerations will be applied to the evaluation of the cytotoxic capacity and function of CD4 *helper* lymphocytes, which will be recorded as positive vs. negative or good vs. weak versus according to the stimulation index.

*2) Analysis of VL increase time above 5,000 copies/mL.*

- The treatment will be stopped in weeks 64-80, if viremia in week 56 is less than in week eight.

- The increase time will be compared (measurement history) with that of other groups (see references 2 and 3)

3) *Multivariant analysis*

A ‘response’ is defined as the lack of a rebound or the absence of indications for ART on multiple occasions following the interruption of treatment.

The indicating response factors will be evaluated by means of multiple regression analysis, and will include:

- CD4 count before ART,

- VL before HAART,

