1.9. Phase of the trial: Phase III

1.10. Primary goal:

To evaluate the virological response, the specific cytotoxic response to HIV and the point of stabilisation of viremia after the fourth cycle of interruption of anti-retroviral treatment (ART), and the proportion of patients who do not require ART at the end of study following the administration of subcutaneous, low doses of IL-2.

1.11. Experimental design:

A single-centre, non-comparative, prospective, open-label, clinical pilot study.

1.12. Disease being studied:

HIV-1 infection.

1.13. Main evaluation variables:

The proportion of patients presenting plasma viral load (VL) three times greater than the base value (prior to ART), or VL >20 copies/mL where base VL <10 copies/mL;

The proportion of patients with good cytotoxic response after the fourth cycle compared with the beginning of the treatment;

The proportion of patients having been administered with IL-2 not requiring ART at the end of the study. (>350 CD4 cells or VL <55,000 copies/mL).

1.14. Test population:

The study will include eight HIV infected, outpatients having begun highly active antiretroviral treatment (HAART) during primary infection.

1. Duration of the treatment:

The treatment will be administered daily from the first interruption of ART with a subcutaneous dose of 125,000 mIU/m2 for six weeks. After completing four cycles of six weeks, the treatment with IL-2 will be stopped. Patient follow-up will be conducted for two years.

1.16. Schedule and anticipated date of conclusion:

The aim is to start the trial, provided authorisation has been obtained, in November 2001. The recruitment period will last two months, and the follow-up will last two years. The aim is to finish the study in December 2003.

***

**2. Contents** page

1. Summary 2

2. Contents 5

3. General information 6

4. Rationale and objectives 8

5. Trial type and design 12

6. Subject selection 13

7. Description of the treatment 15

8. Trial development and response evaluation 17

9. Adverse events 19

10. Ethical aspects 21

11. Practical considerations 22

12. Statistical analysis 23

13. References 25

Annexes:

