**7. Description of the treatment**

Patients will stop antiretroviral treatment for eight weeks and will return to it for eight to twelve additional weeks with the addition of interleukin-2 for six weeks.

This process will be repeated four times. Upon finishing the four cycles, treatment with IL-2 and ART will be suspended unless there has been evidence of viral replication to the point that viral load (VL) reaches a stable level. (Definition of point stabilization: equal VL in three sequential determinations separated by at least three weeks)

a) Doses, intervals, method and form of administration and duration

Interleukin-2 (IL-2), 125,000 units/m2/day, subcutaneously, for six weeks

b) Criteria for modifying the protocol during the trial:

 INTOLERANCE/TOXICITY

Interleukin-2: the tolerance of the medication will be evaluated at each visit with a view to its suspension in cases where the severity or intensity of adverse effects so prescribe.

 SAFETY MEASURES

Because of concerns over an eventual appearance of resistance and a loss of antiretroviral treatment efficacy, various measures have been designed to ensure that intermittent therapy will be immediately discontinued in case there is a failure to:

- Analyse the response to treatment in the weeks leading up to each interruption. VL will be measured at seven weeks after restarting treatment in each cycle. The study will be stopped if more than two favourable responding patients reach VL <50 copies/mL.

- The study will only be interrupted between weeks 64 to 80 in those patients who show lowered VL after the third interruption compared with the first interruption.

- ART will be started in patients with CD4+ lymphocyte count <350 cells/µL or with an HIV-1 plasma VL >55,000 copies/mL in two consecutive determinations (27). In asymptomatic patients with CD4+ lymphocyte count between 350-500 cells/µL and/or VL between the previous levels, the evaluation of resuming ART will be done on an individual basis.

- There will be a safety commission.

c) Concomitant medications:

Any concomitant medication will be reflected appropriately in the DCN (detailing the product, dose, administration method, day of administration, reason for the treatment, etc.).

1. Salvage medication:

ART will be started in patients with CD4+ lymphocyte count <350 cells/µL or with an HIV-1 plasma VL >55,000 copies/mL in two consecutive determinations (27).

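### The viral-load increase outcome has no single reference value or time window, and the set-point rule of three equal values can hardly be met at detectable viral load

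*Protocol*

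**What the plan says.** **Increase in VL.** The Section 1.13 summary counts patients whose VL is "three times greater than the base value (prior to ART), or VL >20 copies/mL where base VL <10 copies/mL". Section 4 (specific aims) and Section 8a repeat the threefold rule over the pre-ART value, without the second limb. Section 12a gives both limbs. The first is "An increase in VL is defined as being at least three times greater than the baseline (prior to ART"), glossed as about 0.5 log. For undetectable patients, "an increase will be considered as being any value >20 copies/mL after two weeks since the interruption of treatment". The heading above both limbs places the assessment in the eighth week after withdrawal.

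**State at each possible baseline.** Section 1.14 describes patients "having begun highly active antiretroviral treatment (HAART) during primary infection", so the pre-ART value is untreated viraemia in primary infection. Inclusion criterion 4 requires VL below 50 copies/mL on treatment for at least eight months. The Section 8 calendar gives an assay limit of 10.

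**Set-point.** Section 7 defines stabilisation as "equal VL in three sequential determinations separated by at least three weeks". Section 12a then evaluates the proportion of patients without an indication for ART "when VL reaches the set-point following the last withdrawal from treatment", and again at the end of the study. Sections 4 and 8a list the level of stabilisation among the aims and main variables.

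**The concern.** The proportion with an increase is one of the main variables, and Section 12a compares it between cycles. If the two limbs rest on different baselines, a patient's classification depends on which limb applies as well as on what the virus did. Two analysts could report different proportions from the same data, each following the text.

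For the set-point, VL is a continuous measurement with assay and biological noise. A rule that asks for equality without a tolerance will seldom be met by a patient whose VL is steady but detectable. An outcome evaluated at the set-point would then describe a selected subgroup, and most stable patients would have no set-point to report.

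**Working it through.** **1. The protocol's own figure.** log10(3) = 0.477, so a threefold rise is about 0.5 log, as stated.

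**2. The second limb under each reading.**
- *Pre-ART base.* In Section 1.13 the base is identified as pre-ART in the same sentence as "VL >20 copies/mL where base VL <10 copies/mL". Untreated primary infection with VL below 10 copies/mL is not realistic, so on this reading the limb is practically empty.
- *On-ART base.* Section 12a names no time for the value below 10 and counts "any value >20 copies/mL after two weeks since the interruption of treatment". That suggests the value at interruption, but it is an inference. On this reading, a patient at 9 copies/mL on ART is judged against 20 copies/mL, while a patient at 11 is judged against three times pre-ART VL.

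**3. Distance between the two thresholds.** No pre-ART VL is given. Assumed range:

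| Assumed pre-ART VL | Threefold threshold | Ratio to 20 copies/mL |
|---|---|---|
| 10,000 | 30,000 | 1,500 |
| 100,000 | 300,000 | 15,000 |
| 1,000,000 | 3,000,000 | 150,000 |

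**4. Relation to the ART-start criterion.** Section 7 starts ART at VL above 55,000 copies/mL in two consecutive determinations. 55,000/3 = 18,333. For any pre-ART VL above 18,333, the threefold threshold is higher than 55,000. Such a patient can meet the VL criterion and restart without being counted as an increase.

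**5. Windows and schedule.** Section 12a uses the eighth week in its heading and after two weeks in the second limb. Section 7 describes eight weeks off treatment. Footnote 1 to the Section 8 calendar describes a first cycle from week 0 to week 10 that begins with two weeks off treatment. On the footnote's schedule, the eighth week after withdrawal falls after treatment has resumed. These passages must be reconciled.

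**6. Chance that a truly stable patient gives three equal values.** Assumptions: log-normal VL, constant median of 500, 5,000, 10,000 or 20,000 copies/mL, within-patient SD of 0.10 to 0.30 log10, and 2,000,000 simulated triples per setting.

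| Meaning of equal | Probability |
|---|---|
| Same copy number | about 1 to 7 per million at 500; none observed at 5,000 or above |
| Same to two significant figures | about 0.01% to 0.55% |
| Same when log10 VL is rounded to 0.1 | about 1% (SD 0.30), 2% (SD 0.20), 8% (SD 0.10) |

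The exception is three values all below the assay limit, which are equal because they are censored. Those patients lie below 10 copies/mL and therefore satisfy the VL criterion of less than 10,000 copies/mL in Section 12a by construction.

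**7. With a tolerance.** If the three log10 values must lie within 0.5, a truly stable patient qualifies with probability 0.95, 0.82 and 0.53 at assumed SDs of 0.15, 0.20 and 0.30.

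**The case against.** A reader might infer that the increase proportion must sit near 0% or near 100% in every cycle. The documents do not support this. With an assumed SD of 0.4 to 0.8 log10, the probability of exceeding three times pre-ART VL is 12% to 28% if rebound centres on the pre-ART level, 0.7% to 11% if it centres 0.5 log lower, and 0.01% to 3% if 1 log lower. The 20-copy limb does give 96% to about 100% for an assumed rebound median of 1,000 to 30,000 copies/mL and SD of 0.6 to 1.0. However, Section 4 also describes patients who stayed controlled off ART, and the trial asks whether such control can be induced. The pooled indicator can therefore vary.

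A reader might also infer that McNemar's test would have almost no discordant pairs. Section 12a words discordance as a higher value in one cycle and a lower value in another, so it does not rest wholly on the increase flag. That inference falls.

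Two further points stand. This is a non-comparative pilot of eight patients with no power claim. Other VL outcomes do not use the flag or the set-point: time above 5,000 copies/mL, viraemia at the end of cycle four and at study end against pre-HAART viraemia, and the ART-indication proportion at study end. Also, the stabilisation definition in Section 7 sits beside a treatment rule, so a new analysis tolerance must not silently change that rule.

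None of this supplies a reference value, a window or a tolerance.

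**Conclusion.** The concern holds in two parts. First, the increase outcome has no consistent reference value or window. The >20 copies/mL limb is either practically empty or tied to a different baseline from the threefold limb. The exact size depends on pre-ART VL, which is not given. The firm figure is the 18,333 copies/mL crossover, above which a patient can meet the VL criterion for starting ART uncounted.

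Second, the set-point rule is practically unattainable for detectable VL: at most about 0.5% at two significant figures, and still only about 1% to 8% if log values are rounded to one decimal, under the assumed SDs. Essentially only patients with three undetectable values receive a set-point, so the set-point proportion is uninformative on its VL criterion.

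These rules are stated in the protocol and give an ambiguous or unusable result if followed, so they are more than detail left to a later plan. They should be corrected, at a severity below must-fix given the pilot size and the other VL outcomes.

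**What to change.** Analysis definitions only:

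- **Between-cycle comparison.** Use log10 VL at one named off-ART time point common to all cycles, taking the last off-ART value if ART restarts earlier. Fix that time point after the sponsor reconciles the interruption length and visit schedule in Section 7, Section 12a and footnote 1 of the Section 8 calendar. Also report the proportion above 5,000 copies/mL, a level Section 12a already uses.
- **Threefold flag, if kept.** Name one reference value and one window for all patients, and state them identically in Sections 1.13, 4, 8a and 12a. Moving the reference to the last on-ART value would make the wording consistent, but nearly every rebound would then count, so the flag should not be the main comparison.
- **Set-point for analysis.** Require three determinations at least three weeks apart whose log10 values lie within a stated tolerance, for example 0.5 log10. Count values below the assay limit as equal. Report patients who restart ART first as not stabilised.

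The treatment wording in Section 7 that refers to a stable level must be reconciled separately by the sponsor. No clinical rule is proposed here.

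The cost is mainly wording, because VL is already scheduled throughout. The downside is that a tolerance will call some slowly drifting patients stable, and at an assumed SD of 0.30 it still misses about 47% of truly stable patients (1 − 0.53).
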